#### Occupational Physical Performance Tests

##### Isometric Mid-Thigh Pull

An isometric mid-thigh pull will be used to measure the lower-body maximal strength. The isometric mid-thigh pull test will be conducted using a military mid-thigh pull rig, and the test will be conducted in line with military procedures. The bar will be fixed at the height of the participants’ mid-thigh while in slight knee and ankle flexion. Participants will step onto the force platform with their thighs touching the bar, shoulders back, and chest up and them looking straight ahead. After stepping onto the platform, participants will be required to stand still for 1 to 2 seconds while their body mass is recorded, and the system is zeroed. Participants will then adopt the pull position and remove the slack from the bar. They will be instructed, on a count of 3, to pull as hard and fast as possible for 5 seconds. Participants will be familiarized with the technique and given 2 practice attempts before completing a maximal pull. Each participant will complete 3 maximal pulls against the fixed bar with a maximal effort for 5 seconds, with a 2-minute rest between attempts. After each attempt, the maximum score taken from the mid-thigh pull display screen will be recorded, and the best of the three attempts will be reported.

##### Seated Medicine Ball Throw

A seated medicine ball throw will be used to assess upper-body power. Participants will sit with their backs pressed against a wall and legs flat to the floor straight out in front of them. The participants will be instructed to push a 4-kg ball from their chest upward and outward at a 45° angle to try and achieve a maximum distance thrown. Participants will be familiarized with the technique and angle of release before testing. The participants will throw the ball once, and the distance achieved will be recorded. All participants will use the same 4-kg ball when performing this test.

##### 2-km Best-Effort Run

A 2-km best-effort run will be used to assess aerobic fitness. Participants will complete 5 laps of a 400-m running track as quickly as they feel comfortable to do so, and the time will be recorded.

##### Vertical Jump

A vertical jump will be used to assess lower-body power. Participants will complete three maximal vertical jumps using a Takei Vertical Jump Meter (Takei Scientific Instrument Co) to determine jump height and estimate leg power. Participants will be instructed to jump as high as possible while keeping their hands on their hips. There will be a 2-minute rest period between attempts, and the best score of the 3 jumps will be recorded. Participants will be allowed time to familiarize themselves with the procedure before starting the test jumps.

### Secondary Outcome Measures

#### Pelvic Organ Prolapse

Pelvic organ prolapse will be measured by a pelvic health physiotherapist at weeks 6, 12, and 24. Vaginal examination will assess for prolapse using the Pelvic Organ Prolapse Quantification system (POP-Q) [39,40], quantifying pelvic support in stages from 0 to 4, with 0 indicating no prolapse demonstrated and 4 demonstrating full procidentia. A total of 6 defined points (Aa, Ba, C, D, Ap, and Bp) and 3 landmarks (genital hiatus, total vaginal length, and perineal body) will be measured using a *POP-Stix* (POPstix) tool. The hymen will be the fixed point of reference throughout the completion of the POP-Q. Each measurement will be taken in centimeters above or proximal to the hymen (positive number), with the plane of the hymen defined as 0 (Table 8) [39]. All measurements, except for total vaginal length, will be performed with maximal Valsalva. The POP-Q staging criteria are listed in Table 9 [39].

**Table 8 table8:** Description of the 9 measures of the Pelvic Organ Prolapse Quantification system.^a^

Points	Description	Range of values
Aa	Anterior vaginal wall 3 cm proximal to the hymen	−3 to +3 cm
Ba	Most distal position of the remaining upper anterior vaginal wall	−3 cm to +tvl
C	Most distal edge of cervix or vaginal cuff scar	N/A^b^
D	Posterior fornix	N/A
Ap	Posterior vaginal wall 3 cm proximal to the hymen	−3 to +3 cm
Bp	Most distal position of the remaining upper posterior vaginal wall	−3 cm to +tvl
gh^c^	Measured from middle of external urethral meatus to posterior midline hymen	N/A
pb^d^	Measured from posterior margin of gh to middle of anal opening	N/A
tvl^e^	Depth of vagina when point D or C is reduced to normal position	N/A

^a^Adapted from Bump et al [39].

^b^N/A: not applicable.

^c^gh: genital hiatus.

^d^pb: perineal body.

^e^tvl: total vaginal length.

**Table 9 table9:** Pelvic Organ Prolapse Quantification system staging criteria.^a^

Stage	Description
0	Aa, Ap, Ba, Bp=−3 cm and C or D≤−(tvl^b^ − 2) cm
1	Stage 0 criteria not met and leading edge <−1 cm
2	Leading edge≥−1 cm but ≤+1 cm
3	Leading edge>+1 cm but <+(tvl − 2) cm
4	Leading edge≥+(tvl − 2) cm

^a^Adapted from Bump et al [39].

^b^tvl: total vaginal length.

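### The POP-Q sign sentence makes positions above the hymen positive, but Tables 8 and 9 require them to be negative

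*Protocol article*

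**What the plan says.** All of the relevant text is in the Protocol article, Secondary Outcome Measures, Pelvic Organ Prolapse. A pelvic health physiotherapist takes the POP-Q measurements at weeks 6, 12 and 24. They comprise six points (Aa, Ba, C, D, Ap, Bp) and three further measures: genital hiatus (gh), perineal body (pb) and total vaginal length (tvl).

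- Sign rule in the text: "Each measurement will be taken in centimeters above or proximal to the hymen (positive number"). The zero follows: "with the plane of the hymen defined as 0 (Table 8"). The text gives no sign for positions below the hymen.
- Meaning of the end stages: "with 0 indicating no prolapse demonstrated and 4 demonstrating full procidentia".
- Table 8, point Aa: "Anterior vaginal wall 3 cm proximal to the hymen". Point Ap: "Posterior vaginal wall 3 cm proximal to the hymen". The ranges for Ba and Bp run from −3 cm to +tvl.
- Table 9, stage 0: "Aa, Ap, Ba, Bp=−3 cm and C or D≤−(tvl^b^ − 2) cm" (the raised b is a footnote mark). Stage 1: "Stage 0 criteria not met and leading edge <−1 cm". Stage 3: "Leading edge>+1 cm but <+(tvl − 2) cm". Stage 2 is the band from −1 to +1 cm, and stage 4 begins at +(tvl − 2) cm.

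**The concern.** The only sign that the text assigns is the reverse of the one on which its staging table depends. The sentence refers the reader to Table 8, so it reads as the key to the tables, yet sentence and tables cannot both be applied to the same woman.

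Direction matters for this outcome. Under Hypothesis in the Discussion, the article expects greater improvement in the training group on every secondary outcome. Under Statistical Analysis, it standardizes outcomes to the baseline SD and runs a principal component analysis on change scores. A record with the wrong sign would enter both with its change reversed. The recruitment target is a minimum of 15 women per group, so even a few such records could matter. Data collection had also begun: by March 2020, four women (two per group) had completed all testing sessions.

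**Working it through.** **1. The sign that the tables imply.**

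- Table 8 locates Aa and Ap 3 cm proximal to the hymen. Table 9 gives these points −3 cm at stage 0, which the text defines as no prolapse. So 3 cm proximal is written −3.
- Stage 0 also needs C or D at or below −(tvl − 2). A well-supported apex is therefore a large negative number.
- Stage 4, full procidentia, is a leading edge at or beyond +(tvl − 2). Positive therefore means distal.
- The Ba and Bp ranges (−3 to +tvl) agree, since the long positive side leaves room for full eversion. The Aa and Ap ranges (−3 to +3) are symmetric and do not settle the sign.

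**2. Inputs for the check.** Table 9 was applied as written. The article gives no tvl, so each whole number from 6 to 12 cm was tried. The leading edge is the anatomically most distal point. Positions below use the tables' sign (proximal negative):

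- Normal support: Aa = Ba = Ap = Bp = −3, C = −(tvl − 2), D = −tvl.
- Stage 1, 2 and 3 examples: Aa = Ba = −2, 0 and +3 respectively, other points normal.
- Full procidentia: Aa = Ap = +3, Ba = Bp = C = D = +tvl.

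**3. Reproducing Table 9 with its own sign.** Normal support meets the stage 0 rule. The three examples have leading edges of −2, 0 and +3 and return stages 1, 2 and 3. For the last, +3 must be below tvl − 2, which is 4 at tvl = 6 and 10 at tvl = 12. Procidentia has a leading edge of +tvl, which is at least tvl − 2, so stage 4.

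**4. The same anatomy with the text's sign.** Every position changes sign:

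| Anatomy | Leading edge, tables' sign | Stage | Leading edge, text's sign | Stage |
|---|---|---|---|---|
| Normal support | −3 | 0 | +3 | 3 |
| Stage 1 example | −2 | 1 | +2 | 3 |
| Stage 2 example | 0 | 2 | 0 | 2 |
| Stage 3 example | +3 | 3 | −3 | 1 |
| Full procidentia | +tvl | 4 | −tvl | 1 |

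For normal support, +3 is above +1 and below tvl − 2 at every tvl tried, so stage 3. The stage 0 wall value of −3 cm is not reproduced. For procidentia, −tvl lies between −12 and −6, which is below −1, and Ba and Bp are not −3, so stage 0 fails and stage 1 results.

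**5. Direction of change.** Take the stage 2 example, in which the anterior wall recovers from the hymen to 3 cm above it. With the tables' sign, Aa and Ba go from 0 to −3 and the stage from 2 to 0. With the text's sign they go from 0 to +3 and the stage from 2 to 3. The signed positions reverse exactly. The stages reverse less exactly: among these examples, 0 and 1 both become 3, and 3 and 4 both become 1, so a change within either pair would disappear.

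**The case against.** The strongest reply is that this is a drafting slip which would reveal itself in use. Staging follows Table 9, which is coherent and sits in the same section. Under the text's sign, normal walls could never meet stage 0, and an examiner would notice that at once. The sentence covers only one direction, which suggests that it is incomplete rather than a deliberate convention. The examiner is a pelvic health specialist. POP-Q is one of many secondary outcomes, and its place first in the list implies no ranking. All of this stands and limits the severity. It does not remove the contradiction, because no other sentence in the article corrects the rule.

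A reader might infer three stronger things that the article does not support:

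- **Normal support would be stage 4.** That needs the leading edge to be the largest signed value, which under the text's sign is D = +tvl. In normal support D is the point furthest above the hymen, so calling it the leading edge is doubtful. The most distal point gives stage 3.
- **The prolapse data cannot be combined.** Nothing shows that assessors differ in the sign they use. A sign reversal that is known can also be undone, and the signs of C and D, normally well above the hymen, would usually show which convention was followed.
- **Women have been staged wrongly.** The article does not show that anyone applied the sentence literally.

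**Conclusion.** The point holds as an internal contradiction in the measurement rule for a secondary outcome. The text makes proximal positive, while Tables 8 and 9 require proximal to be negative and distal to be positive.

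The size is conditional. It applies only if the written sign is used with Table 9, with the most distal point as leading edge and tvl between 6 and 12 cm. In that case normal support becomes stage 3, full procidentia becomes stage 1, and improvement is recorded as worsening. The primary outcome and the sample size do not depend on it. It should be fixed, but it does not threaten the trial's main conclusion.

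**What to change.** Replace the sign sentence with a rule of this kind: the six points Aa, Ba, C, D, Ap and Bp are recorded in centimeters relative to the hymen (0), negative when above or proximal to it and positive when below or distal to it; gh, pb and tvl are recorded as unsigned lengths. The last clause is needed because the present sentence covers every measurement, although Table 8 describes those three as distances and not as positions relative to the hymen.

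Then check the data form and the records already collected for the sign used, and correct any reversed entries before analysis. The cost is one reworded sentence and a check of the form and existing entries. Tables 8 and 9, the visit schedule and the analysis model need no change.

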#### Pelvic Floor Strength

Pelvic floor strength will be measured by a pelvic health physiotherapist at weeks 6, 12, and 24 using the PERFECT (power, endurance, repetitions, fast, every contraction timed) scheme [41]. The participant will perform maximum-effort pelvic floor contraction following instructions and a practice attempt. Power will be recorded on a modified Oxford scale of 0 to 5. Endurance will be assessed by counting the number of seconds until maximum voluntary contraction can no longer be sustained and fatigue is reached. Repetitions of this sustained contraction will be performed with a 4-second rest between each contraction. Fast contractions will be performed by 1-second maximum voluntary pelvic floor contraction and 1-second relaxation until a maximum voluntary contraction can no longer be achieved. Overactivity, coordination, and relaxation of the pelvic floor muscle contraction will also be assessed during the digital vaginal examination.

#### Musculoskeletal Physiotherapy Assessment

Musculoskeletal physiotherapy assessments will be performed by a pelvic health physiotherapist at weeks 6, 12, and 24. *Rectus diastasis* will be assessed by measuring the distance between the internal borders of the *m. rectus abdominis*; fingers will be placed vertically on the *linea alba* 4 cm above and below the umbilicus and at the umbilicus during a curl-up movement. Scoring is an approximation of the width separation and the tone and tension of the *linea alba* structure. The larger the score (cm), the greater the separation of the *m. rectus abdominis*.

At weeks 6, 12, and 24, the pelvic health physiotherapist will observe all participants’ posture, movement patterns, and breathing. If the pelvic health physiotherapist deems participants’ movement or breathing patterns to be dysfunctional, exercises included in the core reconnection and physical development training may be modified slightly or additional advice and guidance provided to ensure that the desired outcome of the exercise is achieved.

Load and impact management tests will be performed during testing session 2, before occupational physical performance tests. These tests will be used to establish the participants’ capacity for safe return to running and further participation in the occupational physical fitness tests [42]. Participants will be asked to perform single-leg balance on each leg (10 seconds), 10 single squats on each leg, a jog on the spot for 1 minute, 10 forward bounds, 10 hops in place on each leg, and 10 single-leg running man motions on each leg. After each functional test, participants will be asked to report any symptoms of pain, heaviness or dragging in the vagina, or incontinence.

#### Pelvic Floor Distress Inventory Questionnaire

The Pelvic Floor Distress Inventory–20 (PFDI-20) [43] will be completed at weeks 6, 12, and 24. The PFDI-20 includes 20 questions and 3 scales. The 3 scales are the Pelvic Organ Prolapse Distress Inventory (6 questions), Colorectal-Anal Distress Inventory (8 questions), and Urinary Distress Inventory (6 questions). Participants will record their answers reflecting on the last 6 weeks and use the scale of 0 to 4 to indicate how bothersome the symptoms are. Each scale is scored from 0 (least distress) to 100 (greatest distress). A scale score will be given according to the mean value of all answered items, with the corresponding scale (possible value 0-4) multiplied by 25 (range 0-100). The sum of the scores from the 3 scales combined, ranging from 0 to 300, provides an overall summary score of the PFDI-20.

#### International Consultation on Incontinence Questionnaire–Vaginal Symptoms

The International Consultation on Incontinence Questionnaire–Vaginal Symptoms [44] will be completed at weeks 6, 12, and 24 and uses 3 subscales to evaluate vaginal symptoms (0-53), associated sexual matters (0-58) and impact on quality of life (0-10) over the previous 4 weeks. There are 14 questions for which participants will record the severity of each symptom. Each item includes a bother scale, where 0 represents the least bothersome in each subscale. The bother scales are not incorporated in the overall score but indicate the impact of individual symptoms.

#### World Health Organization Quality of Life Questionnaire

The World Health Organization Quality of Life-BREF questionnaire [45] will be completed at weeks 6, 12, and 24. Participants will respond to the 26 questions reflecting the last 2 weeks. The World Health Organization Quality of Life-BREF questionnaire provides an overall quality of life and well-being score and allows the calculation of four domain scores: physical health, psychological health, social relationships, and environment.

#### Edinburgh Postnatal Depression Scale

The Edinburgh Postnatal Depression Scale will be completed at weeks 6, 12, and 24. The Edinburgh Postnatal Depression Scale contains 10 questions reflecting the past 7 days [46]. The questionnaire will produce a total score of postnatal depression symptoms (range 0-30) with a score of ≥13, indicating a high likelihood of depressive illness. Participants will be informed that they can omit any questions that they do not wish to answer. However, if >20% of the data are missing for an individual, their data will not be included in the subsequent analysis.

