### Power Calculation

Kraemer et al [62] identified that single-lift strength was 39 (SD 7) kg and 37 (SD 5) kg for women at the end of a 6-month total strength and power and total strength and hypertrophy resistance training protocol, respectively, compared with 32 (SD 4) kg for women undertaking normal field-based military training. Based on the effect sizes between these training and control groups (total strength and power vs control, Cohen *d*=1.23; total strength and hypertrophy vs control, Cohen *d*=1.10), it is anticipated that between 9 and 11 women would be required per group to identify greater posttraining strength in the intervention group than in the control group, with a 1 − β of .80 and α of .05. Hendrickson et al [63] identified that squat and bench press 1 RM were 77 (SD 3) kg and 41 (SD 2) kg, respectively, for women at the end of a 12-week endurance and strength training program, compared with 68 (SD 4) kg and 34 (SD 2) kg for women in the control group, respectively. Based on the effect sizes between the training and control groups (squat, Cohen *d*=2.55; bench press, Cohen *d*=1.62), it is anticipated that between three and six women would be required per group to identify greater posttraining strength in the intervention group than in the control group, with a 1 − β of .80 and α of .05. Hendrickson et al [63], identified that a 3.2-km run time was 18.5 (SD 1.0) minutes for women at the end of a 12-week combined endurance and strength training program, compared with 22.1 (SD 1.2) minutes for women in the control group. Based on the effect sizes between the training and control groups (Cohen *d*=3.26), it is anticipated that 3 women would be required per group to identify greater aerobic fitness in the intervention group than in the control group, with a 1 − β of .80 and α of .05. As such, 11 participants per group would be sufficient to detect improved strength and aerobic fitness in the intervention group compared with the control group. To allow for dropout and noncompliance, we aim to recruit a minimum of 15 participants per group.

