### Statistical Analysis

To maximize statistical power, outcomes will be analyzed using mixed-effects linear models to leverage the collection of data on more than 2 time points and to facilitate the analysis of unbalanced data based on participant attrition. Participants will be included as random effects, with group and time included as fixed effects, to assess within- and between-group differences over time. Sensitivity analyses will be conducted by including baseline values in models or other data relative to potential confounders to account for nonrandom allocation. Linear models will be structured to assess within- and between-group differences over time (eg, the inclusion of resistance and HIIT exercise), establishing the rate of change of intervention and control and determining whether these rates are distinct. The suitability of the models will be established by assessing model residuals and transformations made if residuals are not normally distributed or homoscedastic. Uncertainty in parameter estimates will be quantified using the Satterthwaite approximation for *df* values or through bootstrapping procedures. To facilitate interpretation of the magnitude of change across different outcomes, analyses will be standardized relative to the baseline SD, thus placing outcomes on a unitless scale. Principal component analysis will be conducted on change scores to investigate the clustering of outcomes relative to the magnitude of change.

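### The EPDS missing-data rule excludes the woman rather than the form, so read literally it discards completed forms that the mixed model could use

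*Protocol article*

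**What the plan says.** The protocol article's section on the Edinburgh Postnatal Depression Scale gives the following:

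- Schedule: "The Edinburgh Postnatal Depression Scale will be completed at weeks 6, 12, and 24".
- Length: "The Edinburgh Postnatal Depression Scale contains 10 questions reflecting the past 7 days".
- Outcome: a "total score of postnatal depression symptoms (range 0-30) with a score of ≥13, indicating a high likelihood of depressive illness".
- Omissions: "Participants will be informed that they can omit any questions that they do not wish to answer".
- Exclusion: "if >20% of the data are missing for an individual, their data will not be included in the subsequent analysis".

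Two other sections bear on this. Under Statistical Analysis, mixed-effects linear models are chosen partly "to facilitate the analysis of unbalanced data based on participant attrition". Under Pelvic Floor Distress Inventory Questionnaire, the PFDI-20 has an explicit rule for incomplete answers: "A scale score will be given according to the mean value of all answered items". The EPDS section has no matching sentence.

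**The concern.** A missing-data rule for a repeated questionnaire has to settle three things: the denominator for the percentage, what is removed when the limit is passed, and how a form within the limit is scored. The EPDS sentence leaves the denominator open (one form, or all three). It sets the removal at the level of the woman. It says nothing about scoring.

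The second of these is the main point. A linear mixed model with a random participant effect can use a woman who contributes one or two of her three forms. A rule that removes her entirely because one form is incomplete discards valid observations before the model sees them. With at least 15 women planned per group, each is up to about 7% of her group (1/15).

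**Working it through.** **Inputs, all from the article.** 10 items; total 0 to 30; three EPDS visits (weeks 6, 12 and 24), so 3 × 10 = 30 answers per woman; limit of more than 20% missing; minimum of 15 women per group (Power Calculation). The article gives no sample size, power or bias figure for the EPDS, so there is none to reproduce.

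**1. When the limit is passed.**
- Counted per form: k/10 > 0.20 requires k ≥ 3. Two omissions (exactly 20%) are accepted.
- Counted over three visits: k/30 > 0.20 requires k ≥ 7. One missed visit gives 10/30 = 33%, which exceeds the limit.

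These are alternatives; one rule cannot have both denominators.

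**2. What is then lost.**

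| Reading | Trigger | Removed | Fits the mixed-model aim? |
|---|---|---|---|
| Per form, woman removed | 3 items on one form | all her EPDS forms | No |
| Pooled, woman removed | 7 of 30 items, or one missed visit | all her EPDS forms | No |
| Per form, form removed | 3 items on one form | that form only | Yes |

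The third reading needs the individual in the sentence to be replaced by the form. The readings also disagree about the same woman. With 3 items omitted at one visit and none elsewhere, she is removed under the first reading. Under the second she is kept, because 3/30 = 10%.

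**3. Illustrative loss under the first reading.** Let q be the chance that a form passes the limit, with visits independent. Both are assumptions; the article gives no rate. The share of women lost is 1 − (1 − q)³. Of 15 women (45 forms) per group:

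| q | Women lost | Of 15 | Forms lost, woman removed | Forms lost, form removed |
|---|---|---|---|---|
| 2% | 5.9% | 0.9 | 2.6 | 0.9 |
| 5% | 14.3% | 2.1 | 6.4 | 2.25 |
| 10% | 27.1% | 4.1 | 12.2 | 4.5 |

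Forms lost are 45 × [1 − (1 − q)³] and 45 × q. In this range the woman-level rule loses roughly three times as many forms.

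**4. Accepted forms with 1 or 2 omissions.** The item maximum is 30/10 = 3, taking items as equally weighted. If omitted items were left out of the sum:
- the understatement would be at most 1 × 3 = 3 or 2 × 3 = 6 points;
- with items missing at random, the total would average 90% or 80% of the full score, so a full score of 13 would average 11.7 or 10.4.

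Scoring as (sum of answered items ÷ number answered) × 10 removes that average shortfall: 10.4 ÷ 8 × 10 = 13.0. For single forms, 11 on 8 items becomes 13.75, and 12 on 9 items becomes 13.3.

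**The case against.** **Context favours the form.** The exclusion follows directly on the permission to leave questions blank, so it most naturally limits omissions on a 10-item form. A missed visit is not an omitted question. This stands as far as it goes: the pooled reading, and with it the 33% figure, is the less natural one. It does not rescue the sentence, because the stated consequence still falls on the individual. Three items skipped once would remove her other forms.

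**Item omission and attrition are different problems.** A completeness limit on forms is compatible with a mixed model for missed visits. That is correct for a form-level limit. A woman-level removal takes out observations that the model could use, whatever caused the gap.

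**Scoring of partial forms may sit in a document not shown.** This stands. A reader might infer that accepted totals are biased low. The article never says that an omitted item counts as zero, so the 3- and 6-point figures are conditional. The PFDI-20 rule does not show that the EPDS is scored differently.

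Other tempting readings also go beyond the text:
- **Depression would look milder, or differ by group.** The article gives no information on which women or items would be missing. Women with diagnosed postnatal depression are excluded at entry. Removal for noncompliance exists only in the intervention group, but it would cost a woman her completed EPDS forms only under the pooled reading.
- **Four of 15 women (27%) would be lost.** The margin between 11 and 15 is a planning allowance for dropout and noncompliance on strength and aerobic fitness outcomes. It does not forecast missed EPDS forms. The 27.1% in the working comes from an assumed q and is unrelated.
- **Women would be misclassified at the cut-off of 13.** The article describes linear models and no analysis of the proportion at or above 13.

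**Conclusion.** The point holds in a limited form. As worded, the EPDS exclusion operates on the woman, and followed literally it removes completed forms from other visits. That runs against the stated purpose of the mixed model. This conclusion rests only on the sentence's own unit and consequence and on the three-visit schedule.

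The size cannot be fixed from the article, because no rate of item omission is given. If 2% to 10% of forms pass the limit, independently across visits, about 1 to 4 of 15 women per group would be lost where form-level removal would cost about 1 to 4.5 of 45 forms. A low bias in accepted totals is not established; it would arise only if omitted items were left out of the sum.

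Severity is low. The EPDS is one of many secondary outcomes, the WHOQOL-BREF also covers psychological health, and the primary outcomes are untouched.

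**What to change.** Replace the exclusion sentence with a rule on these lines: the 20% limit applies to each EPDS form; a form with more than 2 of its 10 items missing is set to missing at that time point only; all other EPDS forms from that woman stay in the mixed model; a form with 1 or 2 items missing is scored as the mean of the answered items multiplied by 10.

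The scoring clause follows the mean-of-answered-items approach already used for the PFDI-20. If the full protocol or the analysis plan already has a scoring rule for partial forms, a cross-reference is enough, and only the unit of exclusion needs changing.

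The cost is one or two sentences, with no change to data collection. The downside is small: proration assumes that skipped items resemble the answered ones, which may fail if women avoid particular questions.
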